### Statistical considerations

#### Sample size

Unlike multi-arm, parallel RCT or comparative experiments, factorial experiments are designed to estimate main effects and their interactions [18]. Each main effect and interaction analysis is, therefore, based upon the total sample size which is chosen to be large enough to detect all primary outcomes [18]; having more factors does not increase total sample size [18]. A total of 480 babies (*n* = 240 per intervention arm) will provide ≥90% power at an overall type 1 error rate of 5% to detect a minimal clinically significant difference in % fat mass at 4 months’ correct age of 3% (lower 95% confidence interval) for parental nutrition and milk supplement interventions, or to detect a reduction in median time to full enteral feeds from 10 to 7 days (hazard ratio 1.43) with the taste/smell intervention. This sample size has assumed a standard deviation of 4% in % fat mass, with Bonferroni corrections to each of the three tests (i.e. alpha per main intervention effect = 0.0167). Allowing for 10% loss to follow-up, we aim to recruit 528 babies (*n* = 66 per randomised condition). The expected effect size is based on an estimated 3% increase in % fat mass in moderate to late preterm infants compared to term infants [7] and an estimated 27% fat mass in term infants at 4 months of age [19]. There are no good data on % fat mass beyond 4 months of age; therefore, this age has been used as the primary outcome.

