#### Statistical analyses

Statistical analyses will be performed using SAS version 9.4 (SAS Institute Inc., Cary, NC, USA). The main intervention effects will be evaluated on an intention-to-treat basis. All eligible infants will be analysed according to the assigned condition at randomisation, adjusting for stratification factors and the non-independence of multiple births. Other baseline confounders that are closely associated with the outcomes will be considered in the model if there is evidence of group imbalance by chance (≥ 10%). For the primary outcomes, % fat mass at 4 months’ correct age will be analysed using generalised linear regression with the model-adjusted mean difference. Time to full enteral feeds will be analysed using Cox proportional hazards model with the adjusted hazard ratio. The between group difference will be estimated with 95% confidence interval and *p*-value. An overall type I error rate of 5% will be maintained controlling for multiple comparisons. Secondary outcomes will be evaluated using regression models appropriate to their distributions with similar model adjustment.

Primary analyses will focus on the main effect of each intervention against its comparator, controlling for co-intervention in the same condition. Secondary analyses will test for possible interactions between the main effects. Additional, per protocol analyses will be conducted on those babies without protocol deviations. Missing data will not be imputed on the study outcomes, as the key assumption of missing at random is unlikely to hold in the analysis populations. Sensitivity analyses will be conducted, however, using a multiple imputations method to explore the potential impact of missing data on the primary outcome.

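### Naming Holm's step-down procedure for the three primary tests would be a cheap gain over a fixed Bonferroni 0.0167, at the same overall 5% error rate

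*Protocol article*

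**What the plan says.** The article has three primary main-effect tests: parenteral nutrition and milk supplement on % fat mass at 4 months' corrected age, and taste/smell on time to full enteral feeds.

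- **Sample size.** "A total of 480 babies (*n* = 240 per intervention arm") are said to meet the power target: "will provide ≥90% power at an overall type 1 error rate of 5" per cent. The calculation is made "with Bonferroni corrections to each of the three tests (i.e. alpha per main intervention effect = 0.0167").
- **Statistical analyses.** "An overall type I error rate of 5% will be maintained controlling for multiple comparisons". No procedure is named here. Results are to be reported as follows: "The between group difference will be estimated with 95% confidence interval and *p*-value".

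No step-down, gatekeeping or alpha-recycling rule appears anywhere in the article. Bonferroni at 0.0167 is therefore the only rule a reader can find, and it is given as a sample-size assumption.

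**The concern.** A fixed Bonferroni split tests each effect at 0.0167 whatever the other two tests show. Holm's procedure orders the three p-values and compares the smallest with 0.05/3, the next with 0.05/2 and the last with 0.05, stopping at the first failure. It needs no added assumption and meets the same overall 5% limit.

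The design makes this worth raising. At the planned effects the two fat-mass tests are almost certain to reject, while taste/smell has the least power in reserve. If the fat-mass tests do reject, Holm passes their share of alpha to the one test that can use it. At stake is a modest, avoidable part of the risk of missing a real taste/smell effect.

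**Working it through.** **Inputs from the Sample size section.** Overall error 5%, three tests; 240 babies per level of each factor; difference 3 points and SD 4 for % fat mass; median time to full feeds falling from 10 to 7 days, so hazard ratio (HR) 10/7, which the article rounds to 1.43.

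**Assumptions.** Tests are two-sided (the article does not say). There are 480 events, meaning every analysed baby reaches full feeds; no event count is given, so 400 and 528 are also shown. The three test statistics are independent, which is reasonable for orthogonal factors. Clustering of multiple births and covariate adjustment are ignored. The 3% carries an unclear bracket about a lower confidence limit and is read here as a true difference of 3 points.

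**Step 1: reproduce the plan's figures.**
- Alpha per test: 0.05/3 = 0.0167; critical z = 2.394.
- Fat mass: SE = 4 × √(2/240) = 0.365; 3/0.365 = 8.2; power = Φ(8.2 − 2.394), above 99.9%.
- Taste/smell: power = Φ(½ × √480 × ln(10/7) − 2.394) = Φ(3.907 − 2.394) = 93.5%. With HR 1.43 it is 93.6%.

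Both exceed 90%, so the stated power holds.

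**Step 2: taste/smell power at each alpha level that Holm can reach (HR 10/7).**

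| Events | 0.0167 (z 2.394) | 0.025 (z 2.241) | 0.05 (z 1.960) |
|---|---|---|---|
| 400 | 88.0% | 90.7% | 94.6% |
| 480 | 93.5% | 95.2% | 97.4% |
| 528 | 95.6% | 96.8% | 98.4% |

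**Step 3: taste/smell power under Holm, 480 events.** The unrounded powers are 0.9349, 0.9521 and 0.9742.
- Both fat-mass effects 3 points: both reject almost surely, so taste/smell is tested at 0.05, giving 97.4%.
- One fat-mass effect 3 points, the other null: taste/smell rejects at 0.025, or at 0.05 if the null test happens to pass 0.025. That is 0.9521 + 0.025 × (0.9742 − 0.9521) = 0.9527, or 95.3%.
- Neither real: extra rejections need a false positive elsewhere. The chance that at least one of two null tests passes 0.0167 is 1 − (1 − 0.0167)² = 0.033. Then 0.9349 + 0.033 × (0.9521 − 0.9349) = 0.9355, a gain of less than 0.1 point.

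With 400 events the same steps give 88.0% under Bonferroni, and 94.6%, 90.8% and 88.1% under Holm.

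**Step 4: error rates.**
- All three null: 1 − (1 − 0.0167)³ = 4.9% under either rule. The two rules make a first rejection on the same condition, so the chance of at least one rejection is always equal.
- Taste/smell null, both fat-mass effects real: Bonferroni tests it at 0.0167 and errs 1.7% of the time. Holm tests it at 0.05 and errs up to 5%.

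**The case against.** The strongest reply is that nothing here is wrong. Bonferroni is valid, 0.05/3 is computed correctly and the power claim reproduces. The 0.0167 is a planning input, the analysis section leaves the procedure open, and a statistical analysis plan that is not shown may already name one. All of this stands, and it is why the point is an improvement only.

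A second reply also stands. The three tests concern separate interventions, with outcomes read at different times. Bonferroni lets each be decided alone. Under Holm the taste/smell conclusion can depend on fat-mass results obtained at 4 months' corrected age, and a team may reasonably prefer independent conclusions. Intervals that match Holm decisions are also less simple than Bonferroni intervals, although the article announces 95% intervals, which do not match a test at 0.0167 either.

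Three stronger readings are tempting and are not supported.

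- A reader might see a contradiction between the Bonferroni split and the statement that "having more factors does not increase total sample size". That sentence describes a general property of factorial designs, in which every main effect uses the whole sample, and the same section then openly sizes for three corrected tests. Holm would not remove any such tension, since its first step is also 0.05/3.
- A reader might infer that the Bonferroni split buys no error control at all. Step 4 shows otherwise: when both fat-mass effects are real, a null taste/smell test errs 1.7% of the time under Bonferroni and up to 5% under Holm. What is true is that both rules respect the stated 5% limit.
- Larger gains can be produced by assuming a weaker hazard ratio or fat-mass differences well below 3 points. The article plans for no such effects, so those gains should not be used to size the point.

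**Conclusion.** The point holds as a low-cost improvement. Holm gives the same overall 5% guarantee as the only rule stated and never rejects less.

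At the planned effects the gain falls on taste/smell alone, because the fat-mass tests already exceed 99.9%. It is 97.4 − 93.5 = 3.9 points if both fat-mass effects are 3 points, 95.3 − 93.5 = 1.8 points if one is, and essentially nothing if neither is. The upper figure is the favourable case, since it needs both nutrition factors to reach the full planned difference. With 400 events the largest gain is 94.6 − 88.0 = 6.6 points, and Bonferroni power would then sit just below 90%. The article gives no event count, so this does not show that the trial is underpowered. All figures assume two-sided tests and ignore clustering of multiple births.

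**What to change.** Add one sentence to the Statistical analyses section, or to the analysis plan if it does not already contain one, before the data are analysed. It should state that the three primary main-effect p-values will be tested by Holm's step-down procedure (0.0167, 0.025, 0.05) at an overall two-sided 5%. Keep the sample-size calculation at 0.0167 as a conservative basis, because that power does not depend on what the other tests show.

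The same text should say that the taste/smell decision is final only once the 4-month fat-mass results are available, and how the reported intervals relate to the tests. No extra babies or data are needed. If the team prefers each question to be decided alone, it should instead state in the analysis section that 0.0167 applies to each test, so that the rule is explicit.

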**Methods/design:**

The DIAMOND trial is a multi-centre, factorial, randomised, controlled clinical trial. A total of 528 babies born between 32^+ 0^ and 35^+ 6^ weeks’ gestation receiving intravenous fluids and whose mothers intend to breastfeed will be randomised to one of eight treatment conditions that include a combination of each of the three interventions: (i) intravenous amino acid solution vs. intravenous dextrose solution until full milk feeds established; (ii) milk supplement vs. exclusive breastmilk, and (iii) taste/smell given or not given before gastric tube feeds. Babies will be excluded if a particular mode of nutrition is clinically indicated or there is a congenital abnormality.

*Primary study outcome:* For parenteral nutrition and milk supplement interventions, body composition at 4 months’ corrected age. For taste/smell intervention, time to full enteral feeds defined as 150 ml.kg^− 1^.day^− 1^ or exclusive breastfeeding. *Secondary outcomes:* Days to full sucking feeds; days in hospital; body composition at discharge; growth to 2 years’ corrected age; development at 2 years’ corrected age; breastfeeding rates.

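### At the stated 10% loss, recruiting 528 babies leaves about 475 evaluable, not 480: the target multiplies by 1.1 instead of dividing by 0.9

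*Protocol article*

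**What the plan says.** In the protocol article, the Sample size section starts from the number needed for analysis: "A total of 480 babies", given as 240 per intervention arm. This number is said to provide "≥90% power at an overall type 1 error rate of 5" per cent, with a Bonferroni split over the three main effects, "alpha per main intervention effect = 0.0167". For the body-composition outcome the inputs are a "minimal clinically significant difference in % fat mass at 4 months’ correct age of 3% (lower 95% confidence interval") and a "standard deviation of 4% in % fat mass".

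The section then moves from the number needed to the number recruited: "Allowing for 10% loss to follow-up, we aim to recruit 528 babies", which it gives as 66 per randomised condition. The Methods/design part of the abstract repeats the target: "A total of 528 babies born between". No part of the article defines the 10% as anything other than loss among the babies enrolled.

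The Statistical analyses section says that missing outcomes are not imputed in the main analysis and that multiple imputation serves only as a sensitivity analysis.

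**The concern.** The number needed, the loss allowed and the number recruited should fit together, and here they do not. The usual slip in this step is to enlarge the evaluable number by the loss percentage instead of dividing it by the proportion retained, and 528 has exactly that form.

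At stake is whether the plan delivers, under its own assumption, the analysed number behind its power statement. Because the primary analysis does not impute outcomes, each baby without a 4-month measurement drops out of the % fat mass comparison. The number retained is therefore the number analysed. A later report judged against 480 would fall short even if follow-up went exactly as planned.

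**Working it through.** **Inputs, all from Sample size:** 480 evaluable babies (240 per level of each factor); loss 10%; 528 recruits (66 in each of 8 conditions); SD 4 percentage points; alpha 0.0167 per main effect; power 90%. The section does not say whether tests are one- or two-sided, so two-sided is assumed.

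**1. Reproducing the plan's figure.**
- 480 × (1 + 0.10) = 528.0, an exact match.
- Per condition: 480/8 = 60, and 60 × 1.1 = 66, also exact.

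**2. The target that leaves 480 after 10% loss.**
- Recruits = evaluable / (1 − loss) = 480/0.9 = 533.3, so 534.
- In equal cells of eight conditions this is 536 (67 per condition).

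**3. What 528 leaves.**
- 528 × 0.9 = 475.2, about 475.
- Per level of each factor: 475.2/2 = 237.6, about 238, against 240.
- Shortfall: 480 − 475 = 5 babies; 5/480 = 1.0%.
- Loss at which 528 leaves 480: (528 − 480)/528 = 48/528 = 9.1%.

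**4. Consequence for % fat mass at 4 months.** The difference detectable with 90% power is (z for alpha + z for power) × SD × √(2/n per level). With z of 2.394 for two-sided alpha 0.05/3 and 1.282 for 90% power, the sum is 3.676.
- n = 240: 3.676 × 4 × √(2/240) = 3.676 × 0.3651 = 1.342 points.
- n = 237.5: 3.676 × 4 × √(2/237.5) = 3.676 × 0.3671 = 1.349 points.

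The change is 0.007 points. If the 3% is a plain difference between levels, 49 babies per level already give 90% power, so 238 against 240 is immaterial. If it is a value that the lower confidence limit must clear, the 1.342 and 1.349 are the amounts by which the true difference must exceed 3 points. The change is then equally small.

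**5. Time to full enteral feeds.** This outcome is reached early in life, so loss before the 4-month visit should hardly touch it. That is a judgement, since the article gives no separate loss figure for it.

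**The case against.** The best defence is that the 10% was meant as an uplift on the evaluable number: 60 per condition plus 10% is exactly 66, and the section does not say in words that 480 will remain. A planned loss of 9.1% rather than 10% is also well inside the uncertainty of any assumed loss rate, and 528 is within about 1% of 534. The point about size stands in full. The point about convention softens the criticism but does not remove it. The text calls the 10% a loss to follow-up, which is naturally a share of those followed, and if an uplift was meant, the loss allowed for is 9.1% and the text should say so. Rounding 533.3 down to a multiple of eight would also give 528, but that too leaves 475.

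Three stronger readings are tempting, and the document supports none of them.

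- *The trial is underpowered, or must enrol more.* A gap of 1% moves the detectable difference by 0.007 points, which does not justify changing enrolment.
- *Power for the feeding outcome falls because of the slip.* That would apply 4-month loss to an outcome reached much earlier. Even if it did apply, power for a hazard ratio of 1.43 by the Schoenfeld formula, counting every baby as an event, would be 93.4% with 475 against 93.6% with 480.
- *The check confirms 90% power at 475.* It does not. The 3% is described as a lower confidence limit with no true difference given, so power for % fat mass under that reading cannot be confirmed at 475 or at 480. The calculations also ignore clustering, although twins and triplets are randomised separately and their dependence is to be adjusted for.

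**Conclusion.** The inconsistency is real and small. The stated evaluable number is not delivered at the stated loss: 528 recruits with 10% lost leave about 475 babies, about 238 per factor level, where the power statement uses 480 and 240.

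The conclusion about the count rests only on reading loss to follow-up as a share of recruits. The size of the consequence for % fat mass further assumes SD 4, two-sided alpha 0.0167, equal factor levels and independent babies. It is a correction of the lowest weight: the figures should agree, but nothing in the design or the planned analysis turns on it.

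**What to change.** Keep the target of 528 and correct the sentence in Sample size in one of two ways:

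- state that with 10% loss about 475 babies (about 238 per factor level) will be evaluable for % fat mass at 4 months' corrected age; or
- state the allowed loss as about 9%, which is the rate at which 528 leaves 480.

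Neither wording should add a fresh assurance about power, for the reasons given above. The abstract needs no change because 528 stays. The cost is one sentence, with no extra enrolment and no change to the analysis.

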#### Statistical analyses

Statistical analyses will be performed using SAS version 9.4 (SAS Institute Inc., Cary, NC, USA). The main intervention effects will be evaluated on an intention-to-treat basis. All eligible infants will be analysed according to the assigned condition at randomisation, adjusting for stratification factors and the non-independence of multiple births. Other baseline confounders that are closely associated with the outcomes will be considered in the model if there is evidence of group imbalance by chance (≥ 10%). For the primary outcomes, % fat mass at 4 months’ correct age will be analysed using generalised linear regression with the model-adjusted mean difference. Time to full enteral feeds will be analysed using Cox proportional hazards model with the adjusted hazard ratio. The between group difference will be estimated with 95% confidence interval and *p*-value. An overall type I error rate of 5% will be maintained controlling for multiple comparisons. Secondary outcomes will be evaluated using regression models appropriate to their distributions with similar model adjustment.

Primary analyses will focus on the main effect of each intervention against its comparator, controlling for co-intervention in the same condition. Secondary analyses will test for possible interactions between the main effects. Additional, per protocol analyses will be conducted on those babies without protocol deviations. Missing data will not be imputed on the study outcomes, as the key assumption of missing at random is unlikely to hold in the analysis populations. Sensitivity analyses will be conducted, however, using a multiple imputations method to explore the potential impact of missing data on the primary outcome.

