MLPT babies inevitably experience a delay between birth and the establishment of full enteral feeds due to immature suck/swallow/breathe coordination, immature gut motility, and delayed supply of sufficient breastmilk. Practices around nutritional support for MLPT babies during this period vary widely as there is little high-quality evidence to guide clinical decision making. The usual practice is to provide intravenous fluids while gradually increasing the volumes of milk given by gastric tube until full enteral feeds are tolerated, and then transitioning to sucking feeds as suck/swallow/breathe coordination matures. However, there are many variations within this general approach. There are no data on whether it is better to start supplemental milk early, either donor milk or formula, or to wait until the mother’s breastmilk is available. Whilst waiting for full milk feeds to be tolerated, there are no data on whether the provision of dextrose alone is sufficient, despite the inevitable catabolism and accumulating nitrogen deficit [10], or whether babies should receive parenteral nutrition containing protein. All of these approaches are in use around the world. A study of nutritional support of 33–35 week gestation late-preterm infants in 10 California and Massachusetts hospitals found the rate of intravenous nutrition use varied from 5 to 66% and the rate of discharge with an enriched formula varied from 5 to 71% [11].

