### Assignment of interventions

#### Allocation sequence generation

Within 24 h of birth, once written consent is obtained, eligible babies will be randomised into one of eight treatment conditions (Table 1) at equal allocation ratio via a secure web-based interface. Randomisation will be stratified by gestation (32^+ 0^ to 33^+ 6^; 34^+ 0^ to 35^+ 6^ weeks), recruitment centre (each centre has different nutrition practices) and sex (this influences growth and body composition), using variable block sizes of 8 or 16. Twins and triplets will be randomised as separate babies.

**Table 1 Tab1:** Factorial design randomisation table. + means the baby receives this intervention; − means the baby does not

Condition	Parenteral nutrition (i)	Milk supplement (ii)	Taste/smell (iii)
1	**+**	**+**	**+**
2	**+**	**–**	**+**
3	**+**	**+**	**–**
4	**+**	**–**	**–**
5	**–**	**+**	**+**
6	**–**	**–**	**+**
7	**–**	**+**	**–**
8	**–**	**–**	**–**

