### Study outcomes

#### Primary outcomes

For parenteral nutrition (i) and milk supplement (ii) factors: body composition assessment at 4 months’ corrected age when infant adiposity is predictive of childhood fat mass [17]. For taste/smell factor (iii), time to full enteral feeds, defined as 150 ml.kg^− 1^.day^− 1^ or exclusive breastfeeding if this occurs prior to enteral feeds of 150 ml.kg^− 1^.day^− 1^ being reached.

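### Gestation is most naturally read as entering the models only as a two-week band; age in days would be more precise for feeding times and hospital stay

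*Protocol article*

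**What the plan says.** Under Allocation sequence generation: "Randomisation will be stratified by gestation", in two bands (32+0 to 33+6 and 34+0 to 35+6 weeks), and also by centre and sex. Under Statistical analyses, babies are analysed as randomised, "adjusting for stratification factors and the non-independence of multiple births". The taste/smell primary outcome has its own sentence: "Time to full enteral feeds will be analysed using Cox proportional hazards model with the adjusted hazard ratio". Secondary outcomes, which include time to full sucking feeds and days in hospital, follow suit: "Secondary outcomes will be evaluated using regression models appropriate to their distributions with similar model adjustment".

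A further route into the model is conditional: "Other baseline confounders that are closely associated with the outcomes will be considered in the model if there is evidence of group imbalance by chance", with a 10% threshold. The article does not state how gestation is coded in the models.

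The Background names immaturity of feeding coordination and of the gut among the causes of delay to full enteral feeds, together with late arrival of the mother's milk. It describes babies first reaching full tube feeds "and then transitioning to sucking feeds as suck/swallow/breathe coordination matures".

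**The concern.** A stratification factor with two levels is naturally fitted as a two-level term. A baby born at 32+0 then has the same gestation value as one born at 33+6, 13 days more mature. The article itself ties time to full enteral feeds and time to full sucking feeds to maturation. For days in hospital the same link is plausible, but it is an assumption here.

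Gestation is known in weeks and days, because eligibility and strata are defined that way, and it is fixed before randomisation. Grouping it discards prognostic information that is already in hand. In a linear model, the within-band differences stay in the error variance. In a Cox model, leaving out part of a strong prognostic factor pulls the estimated treatment hazard ratio toward 1 and costs power. The comparison most exposed is the taste/smell primary outcome, which is tested at alpha 0.0167.

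**Working it through.** **1. The plan's own figure.** Inputs from Sample size: 480 babies, 1:1 on each factor, hazard ratio 1.43 (medians 10 and 7 days; 10/7 = 1.43), alpha 0.0167 (taken as two-sided), power at least 90%. Schoenfeld's formula gives events = 4(z₁₋α/₂ + z₁₋β)²/(ln HR)² = 4(2.393 + 1.282)²/(0.3577)², or 423 events for 90% power. With 480 events, power = Φ(0.3577 × √480/2 − 2.393) = Φ(1.525) = 93.6%. The stated power reproduces.

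**2. What the band leaves.** Assume gestation is spread evenly over the 28 eligible days. The article gives no distribution.
- Total variance: 28²/12 = 65.3.
- Within-band variance: 14²/12 = 16.3, so the SD is 4.0 days.
- Between-band variance: 7² = 49.
- Share captured: 49/65.3 = 75%. Share left: 25%.

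The largest within-band gap is 13 days (days 0 to 13 of a 14-day band).

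**3. Cost in the Cox model.** The article gives no gestation effect on time to full feeds, so a range was assumed. The simulation used 480 babies, even gestation, exponential times, no censoring, a treatment hazard ratio of 1.43 conditional on gestation in days, two-sided alpha 0.0167 and 2,000 replicates. Centre, sex and clustering were left out.

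| Gestation HR per 14 days | Power, band | Power, days | Estimated HR, band | Estimated HR, days |
|---|---|---|---|---|
| 1.0 | 92.8% | 92.9% | 1.43 | 1.43 |
| 1.5 | 91.6% | 92.2% | 1.42 | 1.43 |
| 2 | 91.2% | 93.4% | 1.41 | 1.43 |
| 3 | 88.7% | 93.1% | 1.40 | 1.43 |
| 5 | 81.8% | 92.6% | 1.37 | 1.43 |

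The Monte Carlo standard error of one power figure near 90% is √(0.9 × 0.1/2000) = 0.7 points, so the gap at 1.5 is within noise.

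**4. Under no treatment effect.** With the band, the mean hazard ratio was 1.00 and rejection ranged from 1.1% to 2.1% against a nominal 1.67%, with no trend across gestation effects.

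**5. Sucking feeds and hospital stay.** Assume each outcome falls by b = 0.5 to 1 day per extra day of gestation, with a remaining SD of 5 to 8 days. Neither range comes from the article. The share of residual variance due to within-band gestation is 16.3b²/(16.3b² + SD²):
- b = 1, SD 5: 16.3/41.3 = 39.5%
- b = 1, SD 8: 16.3/80.3 = 20.3%
- b = 0.5, SD 5: 4.08/29.08 = 14.0%
- b = 0.5, SD 8: 4.08/68.08 = 6.0%

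**6. Would the imbalance clause bring days in?** Read the 10% threshold as a standardised difference (an assumption), with bands exactly balanced and 240 per arm. The trigger is 0.1 × √65.3 = 0.81 days. The standard error of the arm difference is 4.04 × √(2/240) = 0.37 days. The ratio is 2.2, so the clause would fire about 3% of the time.

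**The case against.** The strongest answer is that the article never fixes the coding. It says stratification factors are adjusted for, which is standard and valid, and the form of a covariate is a detail that a condensed article may leave to an analysis plan that is not shown here. That stands as a limit on the point. If the analysis plan already uses days, confirming it closes the matter.

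The imbalance clause could in principle admit gestation in days. This stands only in part. The clause speaks of variables other than the stratification factors, it would seldom trigger (step 6), and the precision gained from a prognostic covariate does not depend on imbalance.

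The size is uncertain, and this stands. Up to a gestation hazard ratio of 2 per 14 days the loss is about 0 to 2 points and power stays above 90%. Late milk supply, which is not infant maturity, also delays full enteral feeds. Recruitment is 528. If all 528 contribute events, Schoenfeld power before any attenuation is Φ(0.3577 × √528/2 − 2.393) = 95.7%, against 93.6% with 480.

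A reader might also infer that every model in the trial is affected. The documents do not support that. For two of the three factors the primary outcome is "body composition assessment at 4 months’ corrected age when infant adiposity is predictive of childhood fat mass". That outcome, the growth Z-scores and the 2-year scores are not maturation times. For % fat mass, 240 per arm with a difference of 3 and an SD of 4 gives power above 99.9%.

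**Conclusion.** The point holds as a matter of efficiency for three outcomes: time to full enteral feeds, time to full sucking feeds and days in hospital. It rests on reading the stratification adjustment as the two-level band, which is the natural reading but not an explicit statement. For hospital stay it also rests on an assumed link to maturity.

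With evenly spread gestation, a quarter of the gestational-age variance goes unused. Entering days gains about 0 to 2 points of Cox power if the gestation hazard ratio is at most 2 per 14 days, and about 4 to 11 points at 3 to 5. Nothing in the article says where in that range the truth lies.

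Two stronger readings should be resisted:
- **That the banded analysis is biased or invalid.** Gestation within bands is balanced in expectation by randomisation, and the simulation shows no null bias and no type I error inflation.
- **That the taste/smell comparison is underpowered.** Power falls below 90% only at assumed gestation effects of 3 or more, with 480 events and with 1.43 taken as the effect conditional on gestation in days. The plan derives 1.43 from two overall medians. If it is an effect averaged over gestation, the banded model should roughly keep its planned power, and the use of days would add to it.

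**What to change.** State in the analysis plan that gestational age at birth in days enters as a continuous covariate (linear, or a low-order spline), in place of or in addition to the two-level band, at least in the models for time to full enteral feeds, time to full sucking feeds and days in hospital. Keep the adjustment for centre, sex, co-intervention and multiple-birth clustering as planned, and leave the randomisation strata unchanged. Fix the functional form before allocation is linked to outcomes, so that it does not depend on observed imbalance.

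The cost is one sentence. No new data are needed, because gestation is already recorded in weeks and days, and the covariate precedes randomisation, so including it introduces no bias.
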